##### Help-seeking intentions

Help-seeking intentions will be measured at the 1-week follow-up assessment using an item that asks participants to rate how likely they would be to access help from one of the four support services if they experienced suicidal thoughts in the future. Participants will respond using a 7-point Likert scale ranging from 1 (extremely unlikely) to 7 (extremely likely). Four separate questions will be used to assess this outcome, with a separate question referring to each of the four support services shown. The highest score of the four questions will be used to indicate participants’ intentions to seek help from one of the four support services in the future.

##### Service preferences

Preferences for suicide prevention services will be elicited through a DCE [16, 17]. DCEs are a survey-based method used to understand how people make choices among different service options with varying attributes. DCEs create hypothetical choice situations, where each choice (service or product) is described by a set of attributes (characteristics) and levels. The DCE will allow inferences to be drawn about the relative importance of suicide prevention service attributes by observing the trade-offs that respondents make when choosing their preferred service.

A list of seven service attributes, each with varying levels, has been constructed based on a literature review and refined through interviews with men with lived experience of suicidal thoughts (*n* = 7). The final list of attributes is out-of-pocket cost, service type (i.e. self-help resources, peer support, counselling, healthcare), service mode (i.e. online, phone, face-to-face), waiting time, availability, service environment (i.e. individual or group), and service linkage (i.e. linking to services helping with employment, finances, housing, relationships). Attribute levels will be altered across the scenarios presented and respondents will be asked to choose their preferred hypothetical suicide prevention service. Each scenario will include two suicide prevention services constructed using the seven attributes and an additional option to choose neither. Scenarios will be presented to participants in the format shown in Fig. 3.

**Fig. 3 Fig3:**
[figure not shown]
Example item from the Discrete Choice Experiment

#### Exploratory outcomes

A range of exploratory measures will be used to assess aspects of service awareness and use, as well as key demographic and clinical moderating variables.

##### Prior awareness and use of the four support services

Participants’ awareness and use of the four support services prior to the study will be assessed using two closed-choice questions presented at the post-intervention assessment: (1) ‘Have you heard of any of the following services (MensLine Australia, Mosh, Roses in the Ocean and SANE Australia) before taking part in this study?’ and (2) ‘Have you used any of the following services (MensLine Australia, Mosh, Roses in the Ocean and SANE Australia) before taking part in this study?’ Response options: ‘Yes’ or ‘No’.

##### Support service chosen most frequently

We will evaluate which of the four support services is chosen most frequently by calculating the number of times the link to each support service is clicked at post-intervention.

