## Methods

### Trial design and setting

This is a five-arm randomised controlled superiority trial with three active arms and two control arms. Participant recruitment, administration of study procedures, and data collection will be conducted entirely online. Once enrolled in the study, participants will be randomly assigned to view one of five video message interventions; three of which test evidence-based messaging derived from themes in the prior literature, and two control videos that promote general help-seeking and suicide awareness. After viewing the videos, participants will be presented with a directory containing information about four mental health support services available in Australia, which have been selected for inclusion in this study based on their specialisation in providing mental health support for men, for their national reach, and for their range of service offerings (e.g. online help, telephone support, etc.). The four services are MensLine Australia, Mosh, Roses in the Ocean, and SANE Australia. Participants will be invited to click on a link to one or more of these services to find out more about what the service offers. There are three measurement occasions during the trial: baseline, post-intervention (immediately after viewing the video), and a 1-week follow-up (see Fig. 1).

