#### Primary outcome

##### Help-seeking behaviour

The primary outcome is help-seeking behaviour, operationalised as a click on the link to at least one of the four support services presented to participants (i.e. MensLine Australia, Mosh, Roses in the Ocean, SANE Australia) immediately after the video is shown.

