### Sample size and power

Based on previous empirical studies of mental health service usage, we estimated that 28% of the participants randomised to one of the three target intervention video messages would click on the link of at least one of the four support services (primary outcome). By contrast, we estimated only 8% of participants randomised to one of the two control video messages would click on the link to at least one support service. Accordingly, we calculated that *n* = 76 participants per trial arm (*N* = 380 total) would provide 80% power to detect our effect of interest with a type I error rate of *α* = 0.05.

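### The service men choose most often is ranked by total link clicks, so repeat clicks by one man can affect the ranking; count men instead

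*Protocol article*

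**What the plan says.** The question and its answer stand in one sentence of the protocol article, under Support service chosen most frequently. The question is "We will evaluate which of the four support services is chosen most frequently"; the answer is obtained by "calculating the number of times the link to each support service is clicked at post-intervention". Table 1 lists the outcome among the exploratory measures and gives click-throughs as its assessment.

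The primary outcome, under Help-seeking behaviour, uses the same click data but is yes or no for each man: "a click on the link to at least one of the four support services presented to participants".

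Under Trial design and setting, a man may use several links: "Participants will be invited to click on a link to one or more of these services". No section limits the clicks per link or says that repeats are removed. Assessment schedule gives 72 hours to complete baseline and post-intervention, and Risk management lets men take a break and return.

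**The concern.** The question is about choice, and its natural unit is the man. The stated rule uses the click as the unit. If the platform records every click, a man who opens the same link three times adds three to that service and a man who opens it once adds one. The total then mixes how many men chose a service with how often those men went back to it. With few clickers spread over four services, a handful of repeat clickers could move a service up or down the order.

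At stake is a descriptive statement about which service appealed most. No hypothesis test and no conclusion about the videos depends on it.

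**Working it through.** The article gives no figure for this outcome, so there is none to reproduce. The check is a reading of the definition, followed by an illustration of size.

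**Expected number of clickers.** Sample size and power gives 76 men per arm, with 28% clicking in the three target arms and 8% in the two control arms.
- Target arms: 3 × 76 × 0.28 = 228 × 0.28 = 63.84
- Control arms: 2 × 76 × 0.08 = 152 × 0.08 = 12.16
- Total: 76 of 380 men

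**Why repeats can matter.** Suppose 45% of the 76 clickers choose service A and 40% choose service B (assumed shares).
- Expected men: 0.45 × 76 = 34.2 and 0.40 × 76 = 30.4, a margin of 3.8 men on 64.6 chosen links.
- Suppose 20% of chosen links are clicked again, with a geometric number of extra clicks of mean 2 (variance 2). Extra clicks per chosen link then have mean 0.2 × 2 = 0.4 and variance 0.2 × (2 + 4) − 0.4² = 1.04.
- Given which men chose which service, repeats add noise to the difference in clicks with standard deviation √(64.6 × 1.04) ≈ 8.2 clicks. The expected margin in clicks is 3.8 × 1.4 ≈ 5.3.

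**Simulation for a pair of services.** Each of 76 clickers chooses A and B independently with the stated shares. Each chosen link is clicked again with the stated probability, with geometric extra clicks. Trials with equal counts of men are excluded, and there were 100,000 trials per cell. The entry is the share of trials in which clicks rank the pair differently from men, or tie it.

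| Shares A v B | 20% repeat, mean 2 extra | 10% repeat, mean 1.5 extra | 5% repeat, mean 1.5 extra |
|---|---|---|---|
| 45% v 40% | 20.9% | 14.5% | 11.3% |
| 45% v 30% | 7.1% | 3.7% | 2.5% |
| 50% v 30% | 3.1% | 1.3% | 0.8% |
| 45% v 25% | 2.5% | 1.1% | 0.6% |

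**How much of this is added error.** For 45% v 40%, the share of all trials that put the less-chosen service ahead is:
- counting men: about 24% in each scenario;
- counting clicks: 30.9%, 27.5% and 26.2% in the three repeat scenarios.

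The added error is therefore about 7, 3 and 2 percentage points.

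**All four services together.** A second simulation gave each man one first choice, a 15% chance of also clicking each other link, and 0.1 to 0.5 repeat clicks per chosen link on average (Poisson or overdispersed). Clicks failed to single out the service that led by men in:
- 18% to 37% of runs with equal first-choice shares, where no service truly leads;
- 15% to 30% with shares of 31/27/22/20%;
- 5% to 15% with shares of 40/25/20/15%.

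**After the change.** Each man adds at most one to each service, so repeat clicks cannot affect the ranking.

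**The case against.** The strongest reply is that the sentence may be ordinary shorthand for how often each service was chosen. Removing duplicate clicks is a derivation step that an article leaves to the full protocol or analysis plan. The article also does not describe how clicks are logged; if only the first click on each link is stored, the two counts coincide. The point about logging stands, and it makes the concern conditional. The point about shorthand stands in part. The article is not silent here: it states a rule, and read as written that rule counts clicks.

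A second reply is that little depends on this outcome. That stands. It is exploratory and belongs to neither stated aim. What men value in a service is addressed by the Discrete Choice Experiment, not by this count. Using a different unit from the primary outcome is not in itself a contradiction.

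Two stronger readings are tempting, and the article supports neither. A reader might infer that confidence intervals for the service counts would be too narrow because clicks from one man are not independent; the article plans no interval, test or model for this outcome. A reader might also infer that the trial is likely to name the wrong service because of repeat clicks. That would take the near-tie as typical and leave out the error that remains when men are counted.

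**Conclusion.** The definition does not match its own question, and it should be corrected as a minor point. The mismatch follows from the text. Its practical effect cannot be known from the article, because service shares, repeat-click rates and click logging are all unstated, and every percentage here except the 28% and 8% planning rates rests on assumed values.

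Over the assumed ranges, the choice of unit matters when two services are close and hardly matters when they are clearly apart. Even for the close pair, most of the risk of a wrong order is sampling noise from about 76 clickers, which counting men does not remove. The primary outcome is binary for each man and is unaffected, as are self-reported service use and help-seeking intentions.

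**What to change.** Define the outcome as the number and percentage of men who clicked each service's link at least once, overall and by arm. Give total clicks as a supplement if they are of interest, and state whether the platform logs every click or only the first on each link.

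The cost is one or two sentences. No new data collection should be needed: the primary outcome already requires clicks to be tied to individual men, and Privacy, confidentiality, and data management lists link clicks among the participant data and keeps a unique study ID in the analysis file.

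Counts by arm will be small (at the planning rates 0.28 × 76 ≈ 21 clickers per target arm and 0.08 × 76 ≈ 6 per control arm), so they should be presented as descriptive only.

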##### Acceptability of the video messaging intervention

The Theoretical Framework of Acceptability questionnaire (TFA) [22] will be used to evaluate participants’ perceptions of the acceptability of the video messaging intervention at the post-intervention assessment. The TFA contains eight items to evaluate the acceptability of healthcare interventions according to their different features (e.g. the perceived effectiveness of the intervention, effort required to engage with the intervention, etc.). Participants rate the extent to which they agree or disagree with each item on a 5-point Likert scale. The distribution of scores will be examined and, based on this distribution, either a mean or a median score will be computed. Higher scores indicate greater acceptability of the intervention. Other aspects of acceptability will also be examined at post-intervention using open-ended qualitative questions: ‘What about the video message appealed to you?’ and ‘What about the video message did not appeal to you?’.

##### Time spent viewing the video

Participants can start, stop, and skip the video message at any time. We will capture the total number of seconds of the video that participants viewed.

##### Impact of intervention on participants’ stress

A single stress item from the University of Washington Risk Assessment Protocol (UWRAP) [23] will be used to evaluate the possible adverse effects of the intervention. The UWRAP is a widely used tool for assessing and managing suicide risk. The stress item in the UWRAP is designed to evaluate the level of stress a person is experiencing. The scale ranges from 0 (no stress) to 7 (highest level of stress). The rating is based on an individual’s subjective experience of stress.

##### Demographics

Demographic variables, including age, current relationship status, highest level of education completed, employment status, and geographic location (i.e. postcode), will be collected at baseline.

##### Severity of suicidal ideation and past attempts

The Suicidal Ideation Attributes Scale (SIDAS) [24] will be used to measure the severity of suicidal thoughts in the past month. This will be assessed at the post-intervention assessment. The SIDAS consists of five items that assess the frequency of suicidal thoughts, the controllability of suicidal thoughts, the closeness an individual has come to making a suicide attempt, the level of distress associated with the thoughts, and the impact of these thoughts on daily functioning. Each item is rated on an 11-point scale (0–10). Item two (controllability) is reverse scored. Total scores on the SIDAS range from 0 to 50, with higher scores indicating more severe suicidal ideation. Previous suicide attempts and self-injury will also be assessed using two questions that ask participants to indicate whether they have attempted suicide (a) in their lifetime and (b) in the past 30 days. Participants respond on a 3-point Likert scale: 0 (‘No, never’), 1 (‘Yes, once’), and 2 (‘Yes, more than once’). Participants are also asked to report the date of their most recent attempt.

##### Wellbeing

The Short Warwick Edinburgh Mental Wellbeing Scale (SWEMWBS) [25] is a 14-item self-report scale that will be used to assess mental well-being at the post-intervention assessment. The SWEMWBS asks participants to rate how often they have experienced different thoughts and emotions over the past 2 weeks on a 5-point Likert scale ranging from 1 (‘None of the time’) to 5 (‘All of the time’). Raw item scores are summed and converted to a metric total score using the SWEMWBS conversion table. Total scores range from 7 to 35, with higher scores indicating better mental well-being.

##### Psychological distress

The Kessler Psychological Distress Scale (KTEN) [26] is a 10-item self-report scale that will be used to assess levels of psychological distress at the post-intervention assessment. It consists of ten questions that ask participants about their feelings and experiences over the previous 4 weeks on a 5-point Likert scale, ranging from 1 (‘None of the time’) to 5 (‘All of the time’). The raw item scores are summed, resulting in a total score ranging from 10 to 50. Higher scores indicate higher levels of psychological distress.

##### Loneliness

The Three-Item Loneliness Scale (TILS) [27] will be used to measure self-reported levels of loneliness at the post-intervention assessment. Items ask: ‘How often do you feel that you lack companionship?’ (Relational connectedness); ‘How often do you feel left out?’ (Collective connectedness); and ‘How often do you feel isolated from others?’ (General isolation). Response categories are as follows: 1 (‘Hardly ever’), 2 (‘Some of the time’), and 3 (‘Often’). The raw item scores are summed to compute a total score, with higher scores indicating greater loneliness.

##### Anhedonia

The Snaith-Hamilton Pleasure Scale (SHAPS) [28] will be used to assess anhedonia. It contains 14 items, covering four domains of hedonic experience: interest/pastimes, social interaction, sensory experience, and food/drink. Each item asks participants to rate how much they agree or disagree with statements of hedonic response in pleasurable situations (for example, ‘I would enjoy my favourite television or radio program’) on the basis of their experience in the ‘last few days’. Items are rated on a 4-point Likert scale, ranging from 1 (‘Strongly disagree’) to 4 (‘Strongly agree’). The raw item scores are summed to compute a total score. Scores range from 14 to 56, with higher scores indicating more severe levels of anhedonia [29].

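### The stated SHAPS scoring runs opposite to its stated interpretation (most enjoyment scores as most anhedonic); as a minor second point, the SWEMWBS item count does not match its range

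*Protocol article*

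**What the plan says.** **SHAPS (protocol article, Anhedonia).** On length: "It contains 14 items, covering four domains of hedonic experience". Participants are asked to "rate how much they agree or disagree with statements of hedonic response in pleasurable situations", and the example given is a statement that one would enjoy a favourite programme, so agreement means pleasure. On coding: "Items are rated on a 4-point Likert scale, ranging from 1 (‘Strongly disagree’) to 4 (‘Strongly agree". On scoring: "The raw item scores are summed to compute a total score". On interpretation: "Scores range from 14 to 56, with higher scores indicating more severe levels of anhedonia". The section mentions no reverse scoring. By contrast, the section on severity of suicidal ideation says explicitly that the second SIDAS item is reversed.

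**SWEMWBS (protocol article, Wellbeing).** The scale "is a 14-item self-report scale that will be used to assess mental well-being". Items are coded 1 to 5, summed, and passed through the scale's conversion table. On range: "Total scores range from 7 to 35, with higher scores indicating better mental well-being".

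**Use.** Table 1 lists both scales among the exploratory outcomes, assessed at post-intervention. The Exploratory analyses section allows demographic and clinical variables to enter the outcome models as interaction terms, one moderator at a time.

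**The concern.** An analyst who follows the Anhedonia section literally would build a variable that rises with enjoyment and then report it as rising with anhedonia. The baseline-type description of the sample would be mislabelled. So would any moderator finding: a video effect concentrated in men with little anhedonia would be reported as concentrated in men with severe anhedonia. The Discussion envisages use of effective videos in mass media campaigns, so a reversed statement about who responds could mislead. The mistake would also be hard to see, since the scored values fall inside the stated limits either way.

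For the SWEMWBS, the stated number of items and the stated range do not fit together without a rescaling that the text does not describe. A reader cannot tell whether the item count is a slip or whether a longer form is being shown and then scored by a table meant for something else.

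**Working it through.** **Inputs.** SHAPS: 14 items, codes 1 to 4, raw sum, agreement = enjoyment, higher total = more anhedonia (Anhedonia). SWEMWBS: 14 items, codes 1 to 5, raw sum then conversion table, total 7 to 35 (Wellbeing). For comparison, Kessler scale: 10 items, codes 1 to 5, range 10 to 50 (Psychological distress); SIDAS: 5 items, codes 0 to 10, range 0 to 50 (Severity of suicidal ideation and past attempts).

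**Step 1: reproduce the stated ranges.** The range of a raw sum is (items × lowest code) to (items × highest code).

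| Scale | Calculation | Result | Stated | Agrees? |
|---|---|---|---|---|
| Kessler | 10 × 1 to 10 × 5 | 10 to 50 | 10 to 50 | yes |
| SIDAS | 5 × 0 to 5 × 10 | 0 to 50 | 0 to 50 | yes |
| SHAPS | 14 × 1 to 14 × 4 | 14 to 56 | 14 to 56 | yes |
| SWEMWBS | 14 × 1 to 14 × 5 | 14 to 70 (raw) | 7 to 35 (total) | no |

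**Step 2: direction of the SHAPS.** Let x be the code on each item. The text's total is S = Σx. The total that fits the stated interpretation reverses each item: S* = Σ(5 − x) = 14 × 5 − S = 70 − S, for a man who answers all 14 items.

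| Respondent | S, as written | S* = 70 − S |
|---|---|---|
| Strongly agrees he would enjoy everything | 14 × 4 = 56 | 14 |
| Answers 3 throughout | 14 × 3 = 42 | 28 |
| Answers 2 throughout | 14 × 2 = 28 | 42 |
| Strongly disagrees throughout | 14 × 1 = 14 | 56 |

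The order is fully inverted. S and S* share the range 14 to 56, so a check of minimum and maximum passes under either rule.

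**Step 3: effect on a moderator model.** Write the linear predictor as b0 + b1·T + b2·S + b3·T·S, with T the intervention indicator. Putting S = 70 − S* gives (b0 + 70·b2) + (b1 + 70·b3)·T − b2·S* − b3·T·S*. The interaction keeps its size, standard error and p-value, and only its sign changes. The fit is identical.

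**Step 4: SWEMWBS item count.** With codes 1 to 5, a lower limit of 7 implies 7 ÷ 1 = 7 items and an upper limit of 35 implies 35 ÷ 5 = 7 items. Both limits point to the same number, half the stated 14.

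**The case against.** **The platform may already score the SHAPS correctly.** The intended direction is explicit, and the sentence on range and direction cites a source not available here. A slip in listing the anchors, or an omitted mention of reversal, is at least as likely as a real scoring error. This stands as a limit: a reader might infer that the trial's anhedonia data are being scored backwards, and the document does not show that. It shows only that the written rule does so. The article does not merely leave out a detail, however. It gives item content, anchors, scoring rule and direction, and they cannot all hold.

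**The SHAPS error would be reversible.** This also stands. With complete items it is an exact linear reversal, correctable at any time without loss of data, and it leaves p-values alone. The sign is nevertheless what a reader of a moderator result relies on.

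**Fourteen SWEMWBS items could still end on a 7 to 35 scale.** A reader might infer that 14 items can never give that range, or that the wrong conversion table is being used. The text supports neither. The 7 to 35 limits are given for the total, and a conversion follows the sum; the 14 to 70 calculation applies to the raw sum only. A table could in principle map one onto the other. The name of the scale, its own table and the range all sit together, and only the item count is out of line, so a one-word slip is the likeliest explanation. What remains is a mismatch to reconcile.

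**The reach is small.** Agreed. The Exploratory analyses section names age, severity of suicidal ideation and viewing time as example moderators. The SHAPS and SWEMWBS come in only under its general wording. Neither is among the safety parameters listed under Data monitoring.

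**Conclusion.** The SHAPS description contradicts itself and, followed as written, gives a wrong result: total as written = 70 − intended total, with the full 14 to 56 scale reversed. Nothing elsewhere in the article corrects it. The size is a change of sign in any SHAPS summary or moderator result, with magnitudes and p-values unchanged. This assumes that all items are worded as enjoyment, as the section describes, and that the codes exported are those printed.

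The SWEMWBS point is minor: the stated item count gives a raw sum of 14 to 70, while the stated total range equals the raw range of seven items. It is a mismatch in description, and the article gives no evidence of mis-scoring.

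It would be wrong to carry either point over to the trial's main conclusions. Both scales are exploratory. The click-through primary outcome, the secondary outcomes, the sample size and the listed safety parameters do not use them.

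**What to change.** **SHAPS.** Check the codes in the platform's export. If they match the text (strong disagreement = 1, strong agreement = 4), score each item as 5 minus the recorded code before summing. If the platform already codes strong agreement as 1 and strong disagreement as 4, sum as exported and correct the anchors in the text. Apply one of these and not both, since a double reversal restores the error. Because the range cannot detect a mistake, verify with a test record: strong agreement throughout should give 14 and strong disagreement throughout should give 56.

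**SWEMWBS.** Check how many items the live questionnaire shows, correct the item count or the range so that they agree, and confirm that the conversion table belongs to the form administered.

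The cost is one scoring line, one look at the live questionnaire and a corrected sentence for each scale. No new data are needed, and power is unaffected.
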